## Abstract

**Background:**

The *ShockOmics* study (ClinicalTrials.gov identifier NCT02141607) is a multicenter prospective observational trial aimed at identifying new biomarkers of acute heart failure in circulatory shock, by means of a multiscale analysis of blood samples and hemodynamic data from subjects with circulatory shock.

**Methods and Design:**

Ninety septic shock and cardiogenic shock patients will be recruited in three intensive care units (ICU) (Hôpital Erasme, Université Libre de Bruxelles, Belgium; Hospital Universitari Mutua Terrassa, Spain; Hôpitaux Universitaires de Genève, Switzerland). Hemodynamic signals will be recorded every day for up to seven days from shock diagnosis (time T0). Clinical data and blood samples will be collected for analysis at: i) T1 < 16 h from T0; ii) T2 = 48 h after T0; iii) T3 = day 7 or before discharge or before discontinuation of therapy in case of fatal outcome; iv) T4 = day 100.

The inclusion criteria are: shock, Sequential Organ Failure Assessment (SOFA) score > 5 and lactate levels ≥ 2 mmol/L. The exclusion criteria are: expected death within 24 h since ICU admission; > 4 units of red blood cells or >1 fresh frozen plasma transfused; active hematological malignancy; metastatic cancer; chronic immunodepression; pre-existing end stage renal disease requiring renal replacement therapy; recent cardiac surgery; Child-Pugh C cirrhosis; terminal illness. Enrollment will be preceded by the signature of the Informed Consent by the patient or his/her relatives and by the physician in charge.

Three non-shock control groups will be included in the study: a) healthy blood donors (*n* = 5); b) septic patients (*n* = 10); c) acute myocardial infarction or patients with prolonged acute arrhythmia (*n* = 10).

The hemodynamic data will be downloaded from the ICU monitors by means of dedicated software. The blood samples will be utilized for transcriptomics, proteomics and metabolomics (“*-omics*”) analyses.

**Discussion:**

*ShockOmics* will provide new insights into the pathophysiological mechanisms underlying shock as well as new biomarkers for the timely diagnosis of cardiac dysfunction in shock and quantitative indices for assisting the therapeutic management of shock patients.

## Background

The clinical protocol “*ShockOmics*: Multiscale Approach to the Identification of Molecular Biomakers in Acute Heart Failure Induced by Shock”, (ClinicalTrials.gov identifier NCT02141607) is part of a complex project which combines the observational clinical study described in this manuscript with animal research and *in vitro* experiments to investigate the fundamental mechanisms of acute heart failure (AHF) in circulatory shock. The goals of the project are the identification of novel biomarkers of shock-induced AHF, the formulation of a multiscale approach to the diagnosis and interpretation of the disease, and the design of new technologies and therapeutic strategies for improving the delivery of care in shock patients.

Circulatory shock is a life-threatening clinical condition, characterized by low tissue perfusion and ensuing cellular damage and organ dysfunction, which affects about one third of patients admitted to the intensive care unit (ICU) [1], with very high mortality rates. Four types of shock are commonly defined according to their hemodynamic patterns: hypovolemic shock (e.g., hemorrhagic shock (HS)), cardiogenic shock (CS), distributive shock (e.g., septic shock (SS)), and obstructive shock [1, 2].

Septic shock is the most common form of shock, which can occur as a complication of sepsis caused by infection. Sepsis and ensuing shock are the leading cause of mortality in the ICU, among the top 15 leading causes of death overall, with a reported mortality rate above 40 %, and more than 200,000 deaths per year in the United States only [3–9]. Recent trials have reported lower mortality rates around 30 % [10–12].

Cardiogenic shock is the second most frequent form of shock, caused by sudden heart failure, due for instance to a severe heart attack. Novel technologies (e.g. extracorporeal membrane oxygenation (ECMO)) have contributed to a reduction of the mortality of cardiogenic shock below 50 % [13–15], but its lethality remains extremely high.

Hemorrhagic shock is a form of hypovolemic shock due to blood loss. It occurs in 36–39 % of the victims of trauma resulting from accidental injuries, which is the leading cause of death at the age between 1 and 44 in the U.S.A. [16, 17].

A frequent consequence of circulatory shock is the development of multiple organ failure (MOF), a condition in which organs not directly affected by the original insult become dysfunctional and eventually contribute to poor outcome. In the specific case of the heart, its function can be directly impaired by cardiac disease, such as acute myocardial infarction or prolonged arrhythmias, which causes cardiogenic shock and low cardiac output. However, in the other forms of shock, the heart can fail in the general context of MOF [18, 19]. Although the goal of restoring an adequate level of perfusion is to prevent any organ from failing, the protection of the heart and the preservation of its function are instrumental for ensuring hemodynamic stability, and an adequate perfusion of all vital organs.

The relationship between shock, hypotension and hemodynamic instability, inflammation and MOF has been extensively investigated, but the mechanisms that ultimately trigger molecular and cellular injury which cause tissue and organ dysfunction remain largely undetermined, so that there is no clear therapeutic target. Hence, current therapies are targeted to restoration of hemodynamic variables and reduction of symptoms of shock/MOF, but they are unable to act at the “beginning of the cascade”.

Vital signs available from measurements or estimates in critical care settings, such as electrocardiogram (ECG), arterial blood pressure (ABP), central venous pressure (CVP), stroke volume (SV) and cardiac output (CO), pulmonary artery pressure (PAP), pulmonary capillary occluded pressure (PAOP), and photo-plethysmographic (PPG) pulse-oximetry are routinely used for monitoring purposes. They convey instantaneous information on the CV status of the patient, but they cannot accurately predict the occurrence of hypotensive episodes and are often not sufficient to guide a timely and effective Early Goal Directed Therapy [20–22], because of the poor understanding of the pathological cascades characterizing shock [23–34]. As a consequence, the success of any intervention, such as fluid resuscitation, vasopressor therapy and the use of inotropes is limited and depends on the trade-off between their short-term beneficial effect and their potential long-term risk. Fluids may restore blood pressure within minutes, but serious complications such as pulmonary edema may arise thereafter as a consequence of excessive fluid administration, causing alterations in tissue perfusion, delay in organ recovery and prolonged supportive therapies, such as mechanical ventilation. Vasoactive drugs are used to maintain blood pressure but present the risk of increasing the cardiac afterload and/or facilitating the occurrence of arrhythmias. Hence, their use can further stress the heart, potentially hampering its residual functionality [32–34].

In the context of low blood pressure, low flow, and reduced ventricular contractility typical of circulatory shock and hemodynamic instability, careful monitoring of heart function is essential to prevent further tissue hypoperfusion and subsequent organ failure. *ShockOmics* focuses on acute heart failure due to shock, and will explore the presence of biomarkers, which could be related (but not limited) to a cascade of pathogenic phenomena, whose onset is potentially associated to the role of the intestine and of the endocrine glands as a source of powerful mediators for tissue injury [26, 35]. *ShockOmics* aims at investigating the molecular triggers of AHF associated with shock and to identify inflammatory mediators and markers which are activated after an initial insult, with a particular emphasis on the role of uncontrolled proteolytic activity as a major cause of severe tissue injury. To achieve this goal, a systematic analysis of expression levels of transcripts, genes and their protein products, and of peptides generated by proteolysis will be carried out on blood samples obtained from ICU patients hospitalized. Based on the preliminary identification of candidate biomarkers of shock-induced AHF, animal experiments and in vitro studies will further validate the initial hypotheses on the fundamental mechanisms and on the biomarkers of the disease. This approach, besides focusing on new biomarkers of the disease, will aim to define new targets for therapy, in order to overcome the shortcomings of current therapies for circulatory shock. The final outcome of *ShockOmics* will be a multiscale integration of the information from different scales of investigation, from gene expression, to protein synthesis and metabolite expression, to organ specific injury in the heart and hemodynamic patterns characterizing the alteration of CV function in shock. In this framework, an important aspect is the interpretation of  the patho-physiological changes in system level variables, i.e. CV measurements, which are routinely available in emergency departments, ICUs and operating rooms, in function of the fundamental processes of disease.

The objectives of the clinical study included in the framework of the *ShockOmics* project will specifically address the following questions:What are the circulating biomarkers of AHF and subsequent hemodynamic instability?What is the relationship between such biomarkers, the biochemical parameters, and the hemodynamic measurements, which are routinely available in the ICU?What are the regulatory points in the cascade, which could become targets for a cardioprotective therapy against shock?

The expected outcomes of the clinical study will be:Definition of candidate biomarkers by means of cutting edge –omics techniques;Development of an innovative multiscale, systems biology based models to describe the relationship between hemodynamic measurements/waveforms available in ICU/OR/ED and the progression of shock induced AHF;Identification of novel targets for effective cardioprotective therapies to prevent/contrast shock progression;Creation of a complex and detailed database of hemodynamic signals collected from the ICU monitors.

## Methods and design

The *ShockOmics* clinical protocol defines the specifics of a multicenter prospective observational study meant to evaluate molecular mechanisms underlying shock and associated with AHF.

The ICUs involved in the clinical study are located in the following hospitals:Hôpitaux Universitaires de Genève, Université de Genève (Geneva, Switzerland)Hôpital Erasme, Université Libre de Bruxelles (Brussels, Belgium)Hospital Mutua de Terrassa (Terrassa, Spain)

All Institutional Ethical Committees in the three participating institutions approved the clinical protocol.

*ShockOmics* will recruit severe SS and CS patients. Severe HS patients will be also recruited, but their inclusion in the study will be limited to the system level investigation of the features of the hemodynamic signals, while the –omics analyses will not be carried out for this group (see Discussion section).

The study will recruit 90 patients suited for analysis with full data collection available, i.e., well preserved blood samples, high quality hemodynamic recordings, all clinical, anamnestic, diagnostic and prognostic data. The patients will be classified according to existing shock severity scores, such as the Sequential Organ Failure Assessment (SOFA) score and the Acute Physiology And Chronic Health Evaluation (APACHE) II [36]. In particular, the SOFA score will be utilized to set the threshold of shock severity as one of the inclusion criteria of the study (see *Inclusion and Exclusion Criteria*).

### Sample size

The sample size was computed taking into consideration the following assumptions:*ShockOmics* is an exploratory observational study aimed at testing new hypotheses on the molecular mechanisms of shock and consequent secondary organ failure, particularly AHF. Such hypotheses will be further explored and validated in animal models.Incidence of AHF in the population is low (average estimate 1.3 cases/1,000 subjects, increasing with age up to 11.6/1,000 in those aged 85 years and over) [37, 38]. Conversely, MOF and specifically AHF are a frequent and often lethal complication in shock patients. Shock increases re-hospitalization rates, organ failure and associated mortality even after ICU discharge [39]. Therefore, we expect to observe the activation of inflammatory factors and pathogens because of the local and systemic ischemia/reperfusion episodes occurring in shock, with an increased risk of AHF.Based on experimental and preclinical studies, we expect to test the occurrence of uncontrolled proteolytic activity, caused by serine proteases, metalloproteinases and other enzymes.

The sample size of *n* = 90 patients was calculated considering as outcome a quantitative measurement of cardiac function (i.e. cardiac output), and the following parameters: a) an Effect Size (f^2^) of 0.205 (for a strength of association equal to R^2^ 0.17); b) α type I error probability equal to 0.05; c) power = 81 %, using a multiple linear regression; d) 10 predictors tested in the model and giving the effect size.

If the strength of association (R^2^) for the selected set of predictors is equal to 0.20, the Effect Size (f^2^) would increase to 0.25, giving to the study a Power of 89 %, while for models with R2 higher than 0.24 the Power obtained would be higher than 95 %.

The analyses of the blood samples and hemodynamic measurements will entail both analyses of the total sample (*n* = 90), which will allow the identification of common predictors across different types of shock, and of the subgroups of the different types of shock, which will allow to identify specificities associated to the disease etiology. A minimum sample size of *n* = 30 patients is needed per each subgroup in order to identify a set of predictors producing an Effect Size equal to 0.43 (for a strength of association equal to R^2^ 0.30), testing up to 3 predictors, with a Power of 80 %, and type I error α equal to 0.05. A maximum sample size of *n* = 60 patients will enable to identify a set of predictors producing an Effect Size equal to 0.25 (for a strength of association equal to R^2^ 0.20), testing up to 6 predictors with a Power of 80 %, and type I error α equal to 0.05.

In the specific case of hemorrhagic shock not determined by pre-existing pathologies (e.g., trauma patients), we expect the risk factors of low perfusion (i.e., reduced cardiac output) in these patients to be strictly related to shock. HS patients will be considered as reference shock population.

We will use data from septic patients and patients with acute heart disease not in shock together with septic shock and cardiogenic shock patients to conduct logistic regression analysis. Each subgroup analysis will be run on minimum of 40 subjects, allowing to identify single predictors with an Odds Ratio of 2.85 on a binary response variable defined as “shock onset”, with a Power of 83 % and type I error α equal to 0.05.

The sample size was estimated using G*Power 3 Calculator. We estimate that each ICU will recruit *n* = 50 patients in order to reach the above mentioned sample size, considering a drop out rate of ~40 %.

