### Patient groups

#### *Septic shock* (*n* = 60)

Septic shock is defined as sepsis-induced hypotension, characterized by systolic blood pressure < 90 mmHg or a drop of > 40 mmHg from baseline or mean arterial pressure < 65 mmHg, persisting despite adequate fluid resuscitation. Adequate resuscitation will be considered achieved when a volume of at least 30 ml/kg of crystalloids will be administered. Additional fluid resuscitation will be guided using hemodynamic monitoring according to local practices. Subgroup analyses will be undertaken to compare the community-acquired and nosocomial-acquired infections.

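### The shock-type subgroup analyses are sized to detect association within each type, so they cannot by themselves show that a predictor is specific to one type.

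*Protocol article*

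**What the plan says.** The Sample size section gives the two levels of analysis different jobs. The total sample of 90 is the one "which will allow the identification of common predictors across different types of shock". The second level consists of analyses "of the subgroups of the different types of shock, which will allow to identify specificities associated to the disease etiology".

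The section then justifies the subgroup sizes. The smaller is introduced with "A minimum sample size of *n* = 30 patients is needed per each subgroup", for R² 0.30, "testing up to 3 predictors, with a Power of 80 %, and type I error α equal to 0.05". The larger is 60 patients for R² 0.20, "testing up to 6 predictors with a Power of 80" %, also at α 0.05. The Patient groups section sets septic shock at 60 and cardiogenic shock at 30.

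Both calculations concern the association of a predictor set with the outcome inside one group. The logistic regressions described next add non-shock controls and take shock onset as the response, so they contrast shock with no shock, not one shock type with the other. The section describes no comparison of associations between septic and cardiogenic shock.

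**The concern.** To call a predictor specific to one etiology is to say that its association with the outcome differs between etiologies. A test of each group against zero does not address that. An association can be real and equal in both groups, yet reach significance in only one because neither group has power near 100 %.

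The design as stated therefore offers within-type power as support for a between-type conclusion. The sorting of candidate biomarkers into shared and etiology-specific is at stake. If specificity is read from the separate models, a shared biomarker can be reported as belonging to one type, and the stated α of 0.05 does not limit how often that happens.

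**Working it through.** **Inputs.** From the Sample size section: n = 30, 3 predictors, f² 0.43 (R² 0.30); n = 60, 6 predictors, f² 0.25 (R² 0.20); n = 90, 10 predictors, f² 0.205; α 0.05. From Patient groups: septic 60, cardiogenic 30. Assumed, because the documents do not give it: an effect common to both types, with R² ranged from 0.10 to 0.30.

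**1. The protocol's own powers.** For the overall regression test, power = P(F′ > F₀.₉₅), with df₁ = p, df₂ = N − p − 1 and noncentrality λ = f²·N.

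- n = 30, p = 3: λ = 0.43 × 30 = 12.9; power 80.7 % (stated 80 %).
- n = 60, p = 6: λ = 0.25 × 60 = 15; power 79.0 % (stated 80 %).
- n = 90, p = 10: λ = 0.205 × 90 = 18.45; power 80.8 % (stated 81 %).

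The arithmetic reproduces to within about a point. The difficulty lies in what these powers are used to support.

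**2. Whole predictor set, same R² in both types.** The groups are independent, so P(exactly one significant) = P_S(1 − P_C) + P_C(1 − P_S), where P_S and P_C are the septic and cardiogenic powers.

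- R² 0.20: P_S = 0.790, P_C = 0.552. 0.790 × 0.448 + 0.552 × 0.210 = 0.354 + 0.116 = 0.47.
- R² 0.30: P_S = 0.967, P_C = 0.806. 0.967 × 0.194 + 0.806 × 0.033 = 0.188 + 0.026 = 0.21.

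With 3 predictors in both groups the results are almost the same, 46 % and 20 %.

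**3. Single predictor, same slopes in both types.** This was simulated with three equal, independent predictors in each model and a two-sided 0.05 t-test per predictor.

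| R² of the set | Significant in exactly one type, 60/30 | Same, 45/45 | Interaction test falsely positive, 60/30 |
|---|---|---|---|
| 0.10 | 36 % | 36 % | about 5 % |
| 0.20 | 53 % | 49 % | about 5 % |
| 0.30 | 52 % | 45 % | about 5 % |

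At R² 0.20 with 60/30, the 53 % splits into 40 % septic only and 13 % cardiogenic only; the predictor is significant in both types in only 17 %.

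The 53 % can be checked without simulation. Each predictor carries f² = 0.25/3 = 0.083. Then λ = 5.0 on (1, 56) df gives 59 % power in septic shock, and λ = 2.5 on (1, 26) df gives 33 % in cardiogenic shock. 0.59 × 0.67 + 0.33 × 0.41 = 0.53.

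**4. Dependence on strength.** By partial R² of one predictor, in models of 6 septic and 3 cardiogenic predictors, the chance of significance in exactly one type is 45 % at 0.05, 54 % at 0.10, 27 % at 0.20 and 7 % at 0.30. It is at least 30 % from about 0.025 to 0.19 and fades for very strong predictors.

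**5. What a direct test can do.** Take R² 0.20 in septic shock, with one of the three predictors having no effect in cardiogenic shock. The interaction test then has about 23 % power for that predictor by simulation. A normal approximation agrees: √0.083 = 0.289, SE = √(1/60 + 1/30) = 0.224, ratio 1.29, and Φ(1.29 − 1.96) = 0.25. For a single strong predictor (partial R² 0.20, septic only) the ratio is 0.5/0.224 = 2.24 and power is about 61 %.

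**The case against.** The protocol nowhere writes the rule that a predictor significant in one type and not in the other is specific. A reader might infer that rule, but it is not in the text. An analysis plan that is not shown could contain a proper comparison. The study also calls itself exploratory, with hypotheses to be validated in animal models. All of this stands, and it limits the point to what the section says its subgroup analyses and sizes will deliver. That statement remains unsupported: a later plan could add a valid test, but the 80 % figures would still not be powers for specificity.

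Four other tempting readings go too far.

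- **Unequal size as the cause.** Equal groups of 45 still give about 36 % to 49 %. Imbalance mainly decides which type receives the label.
- **Septic predictors with no cardiogenic counterpart.** The counts of 6 and 3 are upper limits in a power calculation, not model specifications.
- **The infection-source comparison.** The septic shock section says "Subgroup analyses will be undertaken to compare the community-acquired and nosocomial-acquired infections". It does not say that predictor associations are what is compared, and the wording is compatible with a direct test.
- **Misdirected therapeutic targets.** The study questions do not tie targets to etiology-specific labels.

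The per-predictor tests in step 3 are also an assumption, since the protocol powers a set of predictors. Step 2 uses its own set-level test, and the conclusion does not change.

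**Conclusion.** The point holds in this limited form: the stated design neither tests nor powers the between-type difference that the subgroup analyses are said to identify. If specificity were read from the separate models, a truly shared predictor would be significant in exactly one type about 36 % to 53 % of the time. The whole set would be so in about 47 % of studies at R² 0.20 and 21 % at R² 0.30. A direct interaction test would err about 5 % of the time per predictor.

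These sizes rest on an assumed common R² of 0.10 to 0.30. The per-predictor figures also assume three equal, independent predictors, and the rate falls below 15 % once a single predictor's partial R² exceeds about 0.25. The pooled analysis may also flag such a predictor as common, but the text gives no rule for reconciling that with a one-type finding. The exploratory purpose softens the consequence, not the logic. The wording should be changed; the trial's data collection and size are not called into question by this point.

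**What to change.** In the Sample size section, base any claim of etiology specificity on the shock-type-by-predictor interaction. Use one model of the 90 patients, with a shock-type main effect and the same predictors for both types, and report each difference in slopes with its 95 % confidence interval. Present the separate n = 60 and n = 30 models as descriptive within-type estimates. State that the 80 % powers apply to association within a type, not to specificity. Whether to adjust for multiplicity across predictors is a matter of choice in an exploratory study and is not part of this request.

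The cost is a change of analysis and wording, with no new patients or measurements. The price is low power: about 23 % per predictor in the case worked above, and about 61 % even for a strong septic-only predictor. Fewer specificities could be claimed, and those claimed would remain exploratory.

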#### Control groups (*n* = 30)

The *ShockOmics* study will also entail the collection of blood samples and hemodynamic data when possible in comparison groups of healthy subjects or patients not it shock:*n* = 5 healthy blood donors will be collected for the purposes of obtaining reference values for proteomics analysis*n* = 10 septic patients not in shock: sepsis caused by infections with inflammatory response with one organ dysfunction at most (as indicated by SOFA sub-scores for specific organ function), without organ support therapy (i.e., mechanical ventilation, renal replacement therapy) and with lactate levels < 2 mmol/L*n* = 10 cardiac patient not in shock, affected by AMI or PA patients

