### Timeline of data collection

Time 0 (T0): admission to the ICU with diagnosis of shock or time of shock diagnosis in patients initially admitted without shock symptoms (see inclusion/exclusion criteria above);Time 1 (T1): time at which the first blood sample for analysis is collected, within 16 h after T0. This time point is considered representative of acute shock before the therapy has taken effect, when shock has already activated the main patho-physiological cascades of inflammation and disease;Time 2 (T2): time at which the first blood sample for analysis is collected, at 48 h after T0. At this time point, the treatment has been administered for a long enough amount of time to evaluate its effects on the early molecular markers of disease;Time 3 (T3): time at which the third blood sample for analysis is collected, on day 7 of the ICU stay of the patient or before discharge from the ICU in case of shorter stays or before discontinuing therapy (death). At this time point, the activated molecular pathways and the relevant system level consequences are assumed to have reached a steady state condition;Time 4 (T4): follow up (FU) on ~ day 100 from Time 0. A blood sample will be collected in survivors who will not be re-hospitalized for the consequences of shock during the time between T3 and T4.

The time course of data collection for the protocol is shown in Fig. 1.

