## Trial status

At the time of publication, 64 patients out of the planned 90 have been recruited, and 12 controls out of 20. The study is expected to be completed by the first quarter of 2016.

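### The logistic regression of shock onset compares patients already in shock with non-shock controls, so it can find markers of established shock but not predictors of onset.

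*Protocol article*

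**What the plan says.** The Sample size section of the protocol article describes the analysis: "We will use data from septic patients and patients with acute heart disease not in shock together with septic shock and cardiogenic shock patients" will be entered in a logistic regression. It sets a floor for each subgroup: "Each subgroup analysis will be run on minimum of 40 subjects". The sensitivity claimed for that size is given as "allowing to identify single predictors with an Odds Ratio of 2.85 on a binary response variable" called shock onset, and the operating figures as "with a Power of 83 % and type I error α equal to 0.05". The software is named as G*Power 3. The scale of the odds ratio, the share of cases, the sidedness and the method option are not given.

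Timeline of data collection sets T0 at ICU admission with a shock diagnosis, or at the diagnosis itself if shock develops later. T1 is the "time at which the first blood sample for analysis is collected, within 16 h after T0". The same section says that by T1 the main disease pathways have already been set in motion.

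The Control groups section under Patient groups lists 5 healthy donors, 10 septic patients and 10 cardiac patients, the last two groups not in shock. The septic controls have at most one organ dysfunction, are "without organ support therapy (i.e., mechanical ventilation, renal replacement therapy) and with lactate levels < 2 mmol/L". The cardiac controls carry no such limits. The heading of that section reads "Control groups (*n* = 30"), and Trial status reports "12 controls out of 20".

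**The concern.** A model of onset needs predictors measured before the event, in people who may or may not go on to have it. Here the cases enter with the event already present, and the controls are selected for not having it. A protein or transcript that rises because of hypoperfusion, fluids or vasopressors would look the same in this regression as one that precedes shock. The study seeks biomarkers for timely diagnosis (Abstract, Discussion) and targets for cardioprotective therapy (Background, objectives), so reading consequences as precursors would mislead where it matters most.

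A second issue follows from selection. If a variable that was used to form the groups is offered as a predictor, its association with the response is built in. It may separate the groups completely, in which case the ordinary maximum-likelihood estimate does not exist.

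**Working it through.** **1. Timing of the samples against the event**

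| Group | Status at entry | First sample | Later shock recorded as an outcome? |
|---|---|---|---|
| Septic shock (60), cardiogenic shock (30) | In shock; T0 is the shock diagnosis | T1, after T0, up to 16 h | Not applicable |
| Septic controls (10), cardiac controls (10) | Selected as not in shock | Same sampling criteria as the patients | No |

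No pre-shock sample is scheduled for any case. The septic shock definition also requires hypotension that persists after a set fluid volume, so some treatment precedes the diagnosis. The response that these data can support is shock present at T1, yes or no.

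**2. Variables that define the groups**

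- Septic model, 60 versus 10. Lactate is below 2 mmol/L in the controls and at least 2 mmol/L in the cases. The case limit stands in the abstract but not in the inclusion list of the main text. If it applies, entry lactate separates the groups completely. SOFA must exceed 5 in cases, while controls may have at most one organ dysfunction, so organ-dysfunction items are strongly tied to group. Hypotension is part of the case definition.
- Cardiogenic model, 30 versus 10. Blood pressure and cardiac index are part of the case definition. No lactate or organ-support limit is stated for the controls.

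**3. The 83% power**

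Inputs from the protocol: n = 40, odds ratio 2.85, α = 0.05. The 40 matches 30 cardiogenic shock patients + 10 cardiac controls; the septic model would have 60 + 10 = 70. Assumptions: one normal predictor, odds ratio per SD, two-sided test unless noted.

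Hsieh approximation: power = Φ(√(n·p·(1−p)) · ln OR − 1.96), with ln 2.85 = 1.047.

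- 30 versus 10 (p = 0.75): √7.5 × 1.047 − 1.96 = 0.908, power **81.8%**.
- 20 versus 20 (p = 0.50): √10 × 1.047 − 1.96 = 1.352, power **91.2%**.
- The case share that gives exactly 83% is p = 0.738, close to 0.75.

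Demidenko formula with variance correction (correction weight 0.85, an assumption):

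- 30 versus 10: 76.4% two-sided, 83.5% one-sided.
- 20 versus 20: 82.1% two-sided.
- With weight 0.75, the last two become 82.4% and 80.7%.

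So 83% can be approached from either allocation, and the planned 30 versus 10 is one of them.

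Simulation at 30 versus 10 (fixed group sizes, two-sided 0.05):

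| Odds ratio 2.85 per | Wald test | Likelihood-ratio test |
|---|---|---|
| Overall SD | 68–69% | 74–76% |
| Within-group SD | 76–77% | 82–83% |

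**4. Control counts**

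5 + 10 + 10 = 25, against 30 in the heading. The two patient control groups give 10 + 10 = 20.

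**The case against.** The strongest reply is that the onset point is one of naming. The protocol says openly that shock is established at T1, calls the study exploratory and sends its hypotheses to animal models. Nowhere does it promise to follow controls until they convert. That is fair, and it limits the remedy to wording and interpretation. It does not remove the problem: the response is defined in the text as onset, and results reported under that name claim more than the design can give. Patients who develop shock after ICU admission do not help, because their T0 is also the diagnosis. History items such as comorbidities do precede shock, but the blood markers that the study is about do not.

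It can also be said that no group-defining variable is named as a predictor, and that predictor lists belong in the analysis plan. This stands in part: the harm is conditional. Since the objectives relate biomarkers to routine biochemical and hemodynamic measurements, a short exclusion is a sensible safeguard.

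Three stronger readings are tempting and are not supported:

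- A reader might infer that 83% was computed for balanced groups. The Hsieh figure of 81.8% at 30 versus 10, against 91.2% if balanced, shows that this cannot be concluded. A shortfall in simulated power depends on an assumed scale and test.
- A reader might apply the lactate and organ-support limits to the 30 versus 10 model. They are stated for septic controls only. Cases in neither model are required to be on organ support, so ventilation does not define them.
- A reader might count the status figure of 20 as a further contradiction. It matches the two patient control groups without the five donors.

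**Conclusion.** The response is wrong as written. With every case sampled after diagnosis and controls selected as not in shock, the regression identifies correlates of established shock, and conclusions about onset do not follow. This rests on the protocol's own timeline and group definitions and needs no numerical assumption.

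Exclusion of group-defining variables is a precaution. Complete separation by lactate holds for the septic model only, and only if the abstract's criterion applies.

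The power statement is not shown to be in error. It is incompletely specified: at 30 versus 10, two-sided simulated power runs from about 68% to 82%, assuming a normal predictor, depending on the test and on whether the odds ratio is per overall or within-group SD. The control heading of 30 against a listed 25 is a real but minor error.

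**What to change.** - Redefine the response as shock present at T1 versus non-shock control, and limit conclusions to markers associated with established shock.
- Exclude from the candidate predictors the variables that define the groups: lactate, SOFA or organ-dysfunction items and blood pressure in the septic model; blood pressure and cardiac index in the cardiogenic model.
- Beside the 83%, state the odds-ratio scale, case share, sidedness and method option.
- Change the control heading from 30 to 25 and note that 20 of these are patient controls usable in the regressions.

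The cost is a narrower claim from this analysis and a few sentences of text. No patients, samples or visits are added.
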